#### Sample size estimation

The primary outcome will be a change in patient activation measure (PAM) [11]. Lin and co-authors found an average effect size of 0.33 in a meta-analysis on studies involving patients with chronic disease reporting change in PAM [19]. Also, a difference of 4 points on the PAM scale is considered clinically important and Marshal et al were able to demonstrate that a 5-point difference was significantly associated with higher odds of CD4 count>200, retention, and viral load suppression [20,21]. Following the definitions as outlined in Hooper et al., 2016 [22], assuming an intra- cluster correlation of 0.02 and individual autocorrelation of 0.8, and only low “time by cluster” effects impacting the PAM scores, the study will require a minimum sample size of 27 per cluster to demonstrate a change of 5 point (green lines in Fig 5) in the activation score between the two groups, assuming the same standard deviation as in Marshall et al, 2013 [21] with a power of at least 90% at an alpha of 0.05% [23].

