**Fig 5 pdig.0000380.g005:**
[figure not shown]
Sample size estimation for stepped wedge design.

It is worth noting that the power to demonstrate a difference will be affected substantially by the cluster by time effect. Hemming et al. provided minimal guidance–but did mention a range on that correlation between 0.3 (large effect) to 0.9 (small effect). They strongly suggest a sensitivity analysis on these assumptions, which is provided in Fig 5. Focusing on the green lines, in the presence of high intra-participant variability (individual autocorrelation, IAC) but small time by cluster effects (cluster autocorrelation, CAC), approximately 90% power can be attained with 22 participants per cluster. However, if the time by cluster effect is stronger, power to demonstrate 5 points change drops to 80%. A 10% increase in sample size will be added to account for non-participation, requiring a total of 30 participants per cluster. Based on the above assumptions, the total minimum sample size is therefore estimated at 480. The number of participants lost to follow-up will be monitored throughout the study, and mitigation strategies implemented to accommodate any unforeseen impact by additional recruitment of patients. To compute the sample size for each site, a weighting based on the total AYP will be used. The following formula will be used to obtain a sample for each of the study sites.

$$n_{i}=\frac{N_{i}}{N}$$

where *n_i_* = Sample size for site *i, N_i_* = total AYP in site *i and N* = total AYP in all the study sites

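### The minimum of 27 participants per cluster does not fit the other sample-size inputs, and the alpha, the second figure of 22 and the autocorrelation wording need reconciling with it

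*Protocol article*

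**What the plan says.** All of this is in the Protocol article, Sample size estimation, including the text below Fig 5, unless another place is named.

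- **Size and target:** "the study will require a minimum sample size of 27 per cluster to demonstrate a change of 5 point", with power of at least 90% and an alpha printed as 0.05%.
- **Correlations:** "assuming an intra- cluster correlation of 0.02 and individual autocorrelation of 0.8", with time-by-cluster effects described only as low. No design CAC is given. The text below Fig 5 reports a range from 0.3 (large effect) to 0.9 (small effect) from cited guidance.
- **SD:** "assuming the same standard deviation as in" a cited study. No number is printed.
- **Background:** the plan notes that a meta-analysis "found an average effect size of 0.33 in a meta-analysis on studies involving patients with chronic disease", and treats 4 PAM points as clinically important.
- **Second size:** below Fig 5, "approximately 90% power can be attained with 22 participants per cluster". This is said to apply "in the presence of high intra-participant variability (individual autocorrelation, IAC) but small time by cluster effects". With a stronger time-by-cluster effect, power is said to drop to 80%.
- **Inflation:** 10% is added, giving 30 per cluster and 480 in total.
- **Design:** Table 2 has 16 clusters, three sequences and surveys T0 to T4. The Study population section says the same cohort is measured throughout. Table 4 allocates 6, 6 and 4 clusters, with 186, 170 and 124 participants.

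**The concern.** In a cohort design with an IAC of 0.8, each participant serves largely as his or her own control, so few participants per cluster are needed unless the outcome is very variable. A minimum of 27 for a 5-point difference therefore looks large. Because every input except the SD and CAC is fixed, the SD behind the 27 can be solved for and compared with the 0-100 scale.

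The paragraph is the only basis for the 480 participants and for what the trial can detect. If 27 is not the minimum, the trial may detect differences below the 4 points that the plan calls important, and a reader told that it was sized for 5 would not know it. If the sensitivity statement covers only part of the quoted CAC range, a reader would also underestimate how far power can fall.

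**Working it through.** **Inputs.** From the plan: difference 5, power 90%, ICC ρ = 0.02, IAC = 0.8, m = 27, 16 clusters, 3 sequences, one cohort. Assumed: CAC 0.8 to 1 for a low time-by-cluster effect, a two-sided normal test, and categorical period effects. Varied: 4 or 5 survey rounds, and clusters split 5/5/6 (Table 2) or 6/6/4 (Table 4).

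**What reproduces.** 27 × 1.1 = 29.7, rounded up to 30, and 16 × 30 = 480. The 27 itself cannot be reproduced without the SD, so it is solved backwards.

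**Variance.** In units of SD², cluster-period means have
- variance ρ + (1 − ρ)/m = 0.02 + 0.98/27 = 0.0563
- covariance between periods ρ·CAC + (1 − ρ)·IAC/m = 0.018 + 0.784/27 = 0.0470 at CAC 0.9.

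Generalised least squares with five rounds and a 5/5/6 split gives SE = 0.0427 SD.

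**Implied SD.** For two-sided 5% and 90% power, 1.960 + 1.282 = 3.2415. Then SD = 5/(3.2415 × 0.0427) = 36.1.

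**Check by the closed-form design effect (3 steps, 4 rounds).**
- r = (27 × 0.02 × 0.9 + 0.98 × 0.8)/(1 + 26 × 0.02) = 1.270/1.52 = 0.836.
- Design effect = 1.52 × 9(1 − r)(1 + 3r)/[8(2 + 3r)] = 1.52 × 0.144 = 0.219.
- Equivalent individually randomised N = 432/0.219 = about 1,974.
- SE = 2·SD/√1,974 = 0.0450 SD, so SD = 5/(3.2415 × 0.0450) = 34.3. The four-round least-squares result is also 34.3.

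**SD at which 27 gives exactly 90% power, over the four layouts:**

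| CAC | Two-sided 5% | Two-sided 0.05% |
|---|---|---|
| 1 | 38.0 to 40.7 | 25.8 to 27.7 |
| 0.9 | 33.7 to 36.1 | 23.0 to 24.6 |
| 0.8 | 30.7 to 32.8 | 20.9 to 22.4 |

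A flat spread over 0-100 has SD 100/√12 = 28.9. Every 5% entry exceeds this and every 0.05% entry is below it.

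**27 against 22.** At CAC 0.9 and 5%, 22 per cluster implies SD 31.1 to 33.3. If the SD were 36, 22 per cluster would give 85% (five rounds, 5/5/6), not about 90%.

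**Sensitivity to CAC.** Suppose 27 gives 90% at CAC 0.9, so SD = 36.1. At CAC 0.3 the SE is 0.0637 SD, and power = Φ(5/(36.1 × 0.0637) − 1.96) = Φ(0.21) = about 58%. Starting from 22 per cluster it is about 62%. The printed 80% is reached at a CAC between 0.7 and 0.8 with 27 per cluster, and near 0.7 with 22.

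**If the SD is smaller.** Power for 5 points at two-sided 5% with five rounds. Power and minimum m use a 5/5/6 split and 27 per cluster. The last column uses the 480 participants of Table 4, shared within each sequence in proportion to cluster size.

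| Assumed SD | Power, CAC 0.9 | Power, CAC 0.3 | Minimum m, CAC 0.9 | Difference detectable with 90% power, CAC 0.9 |
|---|---|---|---|---|
| 15 | >99.9% | >99.9% | 4 | 2.1 |
| 20 | >99.9% | 97.5% | 7 | 2.8 |
| 25 | 99.7% | 88% | 12 | 3.5 |

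**The case against.** The strongest reply is that the deciding input is absent. The SD comes from a cited study and the power curves in Fig 5 are not shown, so 27 can be neither reproduced nor refuted outright. That stands, and the result is a mismatch to be explained, not a proven miscalculation.

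The implied SD also depends on choices the plan does not print. With t critical values on 9 to 14 degrees of freedom and CAC 0.8, it falls to about 27 to 31. At CAC 0.7 it is 28 to 30, and at CAC 0.5 it is 25 to 27. But 0.5 is hard to call a low time-by-cluster effect when the quoted range puts the small-effect end at 0.9. The 28.9 is a benchmark and not a ceiling, since scores piled at both ends of the scale would exceed it. Nothing in the plan suggests such a distribution.

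A reader might divide 5 by the cited 0.33, get an SD of about 15 and say that the plan contradicts itself. The document does not support this: the 0.33 is background, and the SD is taken from a different study.

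A reader might also infer from the reversed IAC wording that the autocorrelation was entered wrongly or left out. The wording error is plain, but the document does not show how the 27 was obtained.

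Finally, the plan does not say that benefit will be judged on significance alone, so that risk is one of interpretation and not a stated rule.

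**Conclusion.** The concern holds in a limited form. On a two-sided 5% alpha with low time-by-cluster effects (CAC 0.8 to 1, assumed), 27 per cluster is the minimum for 90% power only at a PAM SD of about 31 to 41, which is hard to credit on a 0-100 scale. On the printed 0.05% the implied SD is about 21 to 28, which is possible. The alpha and the 27 therefore cannot both be right if 5% was meant. The unexplained 22, the reversed description of IAC, and a reported drop to 80% that stops well short of the 58% implied at CAC 0.3 add to the inconsistency.

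It would be tempting to conclude that the stated power is wrong. That is not shown. At two-sided 5%, any SD below the implied value gives more than 90% power for 5 points at the same CAC. The trial would then be larger than it needs to be for 5 points. At assumed SDs of 15, 20 and 25 (CAC 0.9) it would detect about 2.1, 2.8 and 3.5 points, all below the plan's 4-point benchmark.

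**What to change.** - Print the SD and the CAC used, and correct alpha to 5% if that is what was meant.
- Rerun the calculation once with IAC 0.8 entered as an autocorrelation.
- Reconcile 27 with 22 per cluster, and state that a high IAC means low within-person variability.
- Restate the power at 5 points, the smallest detectable difference for 480 participants on the Table 4 allocation, and the power over CAC 0.3 to 0.9.
- Say that the effect estimate and its confidence interval will be interpreted against the 4-point difference.

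The cost is one rerun and a corrected paragraph. No change in enrolment is needed.

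### The sample-size statement prints alpha as 0.05% (0.0005), almost certainly a misprint for 5%, and does not reconcile 27 per cluster as the minimum for 90% power with 22 per cluster for about 90%

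*Protocol article*

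**What the plan says.** All the statements are in the Protocol article, Sample size estimation, before and after Fig 5.

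- **Main statement.** "the study will require a minimum sample size of 27 per cluster to demonstrate a change of 5 point", "assuming an intra- cluster correlation of 0.02 and individual autocorrelation of 0.8", and "only low “time by cluster” effects impacting the PAM scores". The SD is taken from a cited study and not printed as a number. The claim is made "with a power of at least 90% at an alpha of 0.05", followed by a percent sign. Sidedness is not stated.
- **After Fig 5.** The text cites a CAC range of 0.3 (large cluster-by-time effect) to 0.9 (small). It then describes a case with high variability within participants, glossed as the IAC, and small cluster-by-time effects, in which "approximately 90% power can be attained with 22 participants per cluster". If the cluster-by-time effect is stronger, "power to demonstrate 5 points change drops to 80" percent. No IAC or CAC value is attached to the 22 or to the 80%.
- **Carried forward.** The 27 is raised by 10% to 30 per cluster, and 16 clusters give 480.

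**The concern.** There are two separate problems.

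**Alpha.** The one place where the document fixes a significance level prints 0.0005, one hundredth of the usual value. Taken literally, the primary comparison would have to reach p < 0.0005. A reader also cannot tell whether the power was computed at that level or at 5%.

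**27 and 22.** Both figures refer to the 5-point difference and to about 90% power with small cluster-by-time effects. One is called a minimum; the other is five participants lower. The wording that separates them points the wrong way. In a cohort analysis, more variability within a person means a lower IAC, so each participant's repeated measurements cancel less noise and more participants are needed. The 480 rests on the 27, so the basis of the trial's size is unclear until the two are reconciled.

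**Working it through.** **Inputs from the Protocol article:** difference 5 points; ICC 0.02; IAC 0.8; 16 clusters in three sequences of 5, 5 and 6 (Table 2); the same cohort surveyed at T0 to T4 (5 waves).

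**Assumptions:** two-sided test; CAC 0.9 for a low cluster-by-time effect (the small-effect end of the range the article cites); SD unknown, so either solved for or cancelling.

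**Step 1. The plan's own total.** 27 × 1.1 = 29.7 and 27/0.9 = 30.0, so 30 either way; 16 × 30 = 480. This reproduces. From 22, 22/0.9 = 24.4 would give 25 per cluster, so the 22 is not the basis of the 480.

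**Step 2. Alpha.** Power = Φ(δ/SE − z₁₋α/₂). Exactly 90% at two-sided 5% means δ/SE = 1.960 + 1.282 = 3.242. At α = 0.0005 the critical value is 3.481.

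- Power at 0.0005: Φ(3.242 − 3.481) = Φ(−0.239) = 0.405.
- Information needed to restore 90%: (3.481 + 1.282)² / (1.960 + 1.282)² = 2.16 times as much.

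Neither result depends on the SD.

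**Step 3. Model for 27 against 22.** Generalised least squares for a closed-cohort stepped wedge with fixed period effects. For m participants per cluster:

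- variance of a cluster-period mean = SD² [ICC + (1 − ICC)/m]
- covariance between two periods = SD² [ICC·CAC + (1 − ICC)·IAC/m]

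The 27 itself cannot be reproduced without the SD. Solving for the SD at which 27 gives exactly 90% (5%, IAC 0.8, CAC 0.9) returns 36.1 (34.3 if 4 waves are used). With that SD and CAC 0.9, 22 per cluster gives:

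| IAC | Power with 22 |
|---|---|
| 0.3 | 42% |
| 0.5 | 53% |
| 0.7 | 72% |
| 0.8 | 84.8% |
| 0.84 | 90% |
| 0.9 | 97.2% |

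A lower IAC moves power away from 90%; 22 reaches 90% only from an IAC of about 0.84. Alternatively, if 22 gives 90% at IAC 0.8 (SD 33.3), 27 gives 94.0%. At least 90% is then true of 27, but 27 is not the minimum.

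**Step 4. The fall to 80%.**

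- *27 per cluster, IAC 0.8, set to 90% at CAC 0.9:* 84% at CAC 0.8, 78% at 0.7, 67% at 0.5 and 58% at 0.3. Power crosses 80% at a CAC of about 0.74.
- *22 per cluster, IAC 0.3, set to 90% at CAC 0.9 (SD 19.6):* 81.5% at CAC 0.3.

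The second case matches a fall from 90% to about 80% over the cited CAC range. The first, at the planned IAC, falls further. The text does not say which case the sentence describes.

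**The case against.** **The two cluster sizes are not strictly contradictory.** A reader might infer that 27 and 22 cannot both be right. The documents do not support that. One is a claim of at least 90%, the other an approximate figure in a separately worded sensitivity case, and Step 3 shows two ways in which they agree. Even the literal reading is numerically possible: with IAC 0.3 and SD 19.6, 22 gives 90%, and 27 at IAC 0.8 gives over 99%. But then 27 is far from a minimum. What stands is that some word or number needs correcting on every reading.

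**The 80% sentence is not shown to be wrong.** It follows the 22-per-cluster case, and a fall of that size reproduces at IAC 0.3. The article also warns that power depends substantially on the cluster-by-time effect. The 58% at the planned IAC holds only if 27 gives exactly 90% at CAC 0.9, which needs an SD of about 36. For assumed SDs of 15, 20 and 25, 27 per cluster at IAC 0.8 and CAC 0.3 has 99.9%, 97.5% and 88.1% power at 5%.

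**The 41% is conditional too.** With CAC 0.9 and IAC 0.8, 27 per cluster would keep 90% power even at 0.0005 if the SD were about 24.6 or less. So it does not follow that the trial is underpowered, nor that the calculation used 0.0005; only the printed value is known.

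**Unprinted inputs.** The SD has a named source, and Fig 5 or the full protocol may give it together with the IAC and CAC values. Their absence from the article's text is not counted as an error here.

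**Conclusion.** The printed alpha of 0.05% needs correcting. It is the only significance level in the document and almost certainly stands for 0.05. The consequence of a literal reading is 90% power becoming about 41%, if 27 per cluster gives exactly 90% at two-sided 5%.

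The 27 and the 22 are unreconciled rather than impossible. For the same SD and power, the variability wording points to more participants, not fewer. The figures agree if the IAC behind the 22 was about 0.84 or higher (CAC 0.9 assumed), or if 27 is not a minimum.

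The 80% figure needs its scenario stated, because at the planned IAC of 0.8 the fall over the cited CAC range can be larger: 90% to about 58% if 27 gives exactly 90% at CAC 0.9.

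None of this shows that 480 is the wrong total.

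**What to change.** 1. State a two-sided alpha of 5%, and confirm from the calculation files that the power calculation used it.
2. Give the IAC and CAC behind the 27 and behind the 22. Then correct whichever is wrong: the wording on variability within participants (if a high IAC was meant) or the description of 27 as a minimum.
3. State the cluster size, IAC and CAC at which power drops to 80%. If that is not the planned case, add the power for 27 per cluster at IAC 0.8 across CAC 0.9 to 0.3.

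The cost is a check or rerun of the existing calculation and a few reworded sentences. The 480 does not change unless the rerun shows that an alpha other than 0.05 was used.

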**Fig 5 pdig.0000380.g005:**
[figure not shown]
Sample size estimation for stepped wedge design.

It is worth noting that the power to demonstrate a difference will be affected substantially by the cluster by time effect. Hemming et al. provided minimal guidance–but did mention a range on that correlation between 0.3 (large effect) to 0.9 (small effect). They strongly suggest a sensitivity analysis on these assumptions, which is provided in Fig 5. Focusing on the green lines, in the presence of high intra-participant variability (individual autocorrelation, IAC) but small time by cluster effects (cluster autocorrelation, CAC), approximately 90% power can be attained with 22 participants per cluster. However, if the time by cluster effect is stronger, power to demonstrate 5 points change drops to 80%. A 10% increase in sample size will be added to account for non-participation, requiring a total of 30 participants per cluster. Based on the above assumptions, the total minimum sample size is therefore estimated at 480. The number of participants lost to follow-up will be monitored throughout the study, and mitigation strategies implemented to accommodate any unforeseen impact by additional recruitment of patients. To compute the sample size for each site, a weighting based on the total AYP will be used. The following formula will be used to obtain a sample for each of the study sites.

$$n_{i}=\frac{N_{i}}{N}$$

where *n_i_* = Sample size for site *i, N_i_* = total AYP in site *i and N* = total AYP in all the study sites

### Ethical considerations

The AMREF Health Africa ESRC and the respective County health departments have sanctioned this protocol. Every participant involved provided their informed and written consent. For participants aged between 15 to 17 years, the study investigators were granted a waiver for parental consent by the ESRC. This decision was based on several considerations: to avoid unintentional revelation of the HIV status, to enhance the participation rate, and to mitigate selection bias, especially since the study entailed minimal risk to its participants. Additionally, the National commission for Science, Technology, and Innovation (NACOSTI) has provided a research license permitting the execution of the study. Furthermore, this trial has been catalogued in the Pan African Clinical Trial Registry at www.pactr.org (ID: PACTR202303729957231).

#### Participant consent and data privacy protection

To safeguard the privacy and data of our participants, we have implemented several critical measures. First, all study investigators have completed comprehensive online training focused on the ethical protection of human subjects in research. Additionally, every member of the study team with access to participant data will be required to sign strict confidentiality agreements before the study begins.

Ensuring participant privacy is a top priority. Interviews will be carefully conducted behind closed doors in designated rooms within the participating facilities, while focus group discussions (FGDs) will take place in outdoor spaces, strategically located within the facility premises to maintain distance from non-participants. Recruitment into the study will only be finalized after obtaining written informed consent, with face-to-face interviews conducted following this crucial step. We will clearly communicate the potential risks and benefits of participation, reinforcing that involvement in the study is entirely voluntary. Written consent for audio recordings will also be obtained from all FGD participants.

For participants under 18 years, identified as ‘mature minors,’ the informed consent process allows them to consent independently. A waiver of parental consent has been secured to protect their privacy, particularly for adolescents who may have chosen not to disclose their HIV status to their parents.

To further protect participant anonymity, personal identifiers such as names and addresses have been deliberately excluded from all study data collection tools. Instead, we have used only initials and unique study codes. Informed consent and assent forms, along with any hard copy data collection tools, will be securely stored in lockable, restricted-access areas at the enrolling sites. All electronic data capture and storage tools will be fortified with password protection, and data will be meticulously de-identified to ensure the anonymity of our participants.

## Results

This study will assess the impact of myCareHub on patient activation, medication adherence, social engagement and viral load suppression among AYP living with HIV. We anticipate improvements in these areas:

Patient activation—we expect that regular interaction with health diaries, reminders, and screening tools through the myCareHub platform will lead to increased PAM scores in the intervention group, indicating higher levels of patient engagement and activation in managing their health.Social engagement—increased use of online communities through the platform is expected to boost SSQ6 social engagement scores, particularly among those who may face barriers to in-person social interactions.Adherence and viral load suppression—with regular notifications and health management tools, we expect higher medication adherence rates and improved viral suppression among participants who use the portal consistently compared to those in the control group.

## Discussion

The anticipated results highlight the potential of myCareHub to enhance self-management among young people living with HIV. Increased PAM scores would suggest that the portal fosters greater patient activation, while improvements in adherence and viral suppression would confirm its role in supporting clinical outcomes.

Several limitations of the study must be considered. First, selection bias may occur, as participants who are more comfortable with technology might be more likely to engage with the portal, potentially skewing the results. Additionally, confounding factors such as socioeconomic status, access to technology, and health literacy could influence the outcomes. While adjustments will be made during analysis to control for these variables, their impact cannot be entirely eliminated. Another challenge is attrition, as some participants may drop out over time, particularly those with limited access to devices or internet connectivity, which could affect the generalizability of the findings. Technological barriers such as unreliable internet access, compatibility issues with devices, and power outages may also hinder full use of the platform, leading to lower-than-expected engagement and, consequently, a reduced impact on patient outcomes. Finally, the study’s generalizability is limited by its focus on specific counties in Kenya, which may restrict the broader applicability of the findings to other regions or populations.

